## Abstract

**Background:** Diabetic peripheral neuropathy (DPN) characterized by nerve damage is a common and disabling chronic microvascular complication in patients with type 2 diabetic mellitus (T2DM), affecting at least half of patients diagnosed with T2DM. Unfortunately, the current treatment for DPN is not ideal. Traditional Chinese medicine (TCM), with a unique theoretical system, has made outstanding contributions in the treatment of T2DM and related complications. Mudan granule, a Chinese patent medicine, has been previously validated that could ameliorate the symptoms, promote nerve tissue repair, increase nerve conduction velocity (NCV) in patients with DPN. However, the previous studies are of variable quality, which limits the clinical application of Mudan granule. Therefore, we designed a double-blind, randomized, placebo-controlled, parallel-arm, multi-center trial to estimate the safety and efficacy of Mudan granule in conjunction with methylcobalamin in individuals suffering from type 2 diabetic peripheral neuropathy.

**Methods:** This work is conducted as a 14-center, double-blind, randomized, placebo-controlled, parallel-arm trial. In all, 402 subjects (aged 30–70 years) will be recruited and randomized in a 1:1 ratio to an intervention group (*n* = 201; Mudan granule + methylcobalamin) and a control group (*n* = 201; placebo + methylcobalamin). Treatment is administered in 24 weeks cycles without any treatment interruption between cycles. Michigan Diabetic Neuropathy Score (MDNS) as the primary outcome will be evaluated at baseline, 12 weeks during the intervention period, and after 24 weeks of the intervention. Adverse events and safety assessments will be also documented. The analysis of all data will be carried out based on a predefined statistical analysis plan.

**Discussion:** The outcomes from this study will offer important evidence regarding the safety and efficacy that Mudan granule can be used as an alternative and complementary therapeutic intervention in patients with type 2 diabetic peripheral neuropathy.

**Clinical trial registration:** Registered at https://clinicaltrials.gov/. Trial registration number: NCT04711980. Registered January 2021.

## Introduction

Type 2 diabetes mellitus (T2DM), caused by metabolic disturbances, is often linked to long-term complications and has adverse effects on the eyes, kidneys, heart, and nerves (Bergrem and Leivestad, 2001; Chen et al., 2011; Yau et al., 2012; Albers and Pop-Busui, 2014; Zheng et al., 2018), seriously impacting global health. In accordance with the International Diabetes Federation update of 2019 (Saeedi et al., 2019), around 90% of the 463.0 million individuals aged 20–79 worldwide who were affected by diabetes suffered from T2DM in 2019. The global prevalence of T2DM has significantly contributed to a corresponding epidemic of complications. Among the complications, Diabetic peripheral neuropathy (DPN) is the most frequent and disabling chronic microvascular complication in patients with T2DM, presented clinically with loss of sensation, tingling, pain, hyperalgesia, and weakness (Peltier et al., 2014; Callaghan et al., 2020). In addition, DPN significantly contributes to the increased morbidity with diabetic foot ulcers and amputation (Tesfaye et al., 2016; Megallaa et al., 2019), which not only inflicts devastating suffering on individuals and their families but also emerges as a major cause for loss of physical independence and potential years of life (Chammas et al., 2016).

Without successful interventions, impacts on the individual, families and even the whole society would be disastrous. At present, glycemic control and symptomatic relief serve as a cornerstone in the treatment for patients with type 2 diabetic peripheral neuropathy (Hemmingsen et al., 2013; Alam et al., 2020). Although tricyclic antidepressants, serotonin–noradrenaline reuptake inhibitors, and anticonvulsants that act on calcium channels are recommended as first-line treatment (Khdour, 2020
), its therapeutic management remains challenging. Adverse reactions include fatigue, somnolence, dizziness, and peripheral edema are inevitable (Boyle et al., 2012; Author Anonymous, 2015). Therefore, additional therapeutic strategies are required to combat this disease.

Integrative medicine that combines conventional Western medicine withtraditional Chinese medicine (TCM) has gradually become the main approach to treat many diseases. As a vital branch of TCM, Chinese patent medicines have been extensively applied in the clinical field as derivatives of Chinese herbal medicine (Ng et al., 2012; Chen et al., 2014). Chinese patent medicines frequently used alone or in conjunction with western medicine could successfully lower blood glucose levels and relieve symptoms in patients with diabetes and diabetic complications (Lian et al., 2015; Lian et al., 2015).

A clinical study confirmed that Chinese patent medicine (Xuesaitongcapsule) combined with *α*-lipoic acid was effective and safe in the treatment of DPN with qi-deficiency and blood stasis, while also reduced the expression of TNF-α and IL-1β in serum (Zhang and Zhu, 2020). Moreover, a network Meta-analysis evaluating the efficacy and safety of the blood-activating stasis-removing Chinese patent medicines for DPN showed that some Chinese patent medicines combined with methylcobalamin were superior to the treatment of the general and methylcobalamin groups in the sensory and motor conduction velocity of the median nerve (Zuo et al., 2020). Mudan granule, a Chinese patent medicine, consisting of Huangqi (*Astragalus*), Yanhusuo (*Corydalis*), Sanqi (*Panax notoginseng*), Chishao (*Radix paeoniae rubra*), Danshen (*Salvia miltiorrhiza*), Chuanxiong (*Ligusticum chuanxiong hort*), Honghua (*Carthamus tinctorius*), Sumu (Logwood), and Jixueteng (*spatholobi Caulis*) has been investigated to be beneficial clinically and experimentally in the treatment of DPN (Wu, 2021; Li, 2020). One of the clinical studies with 60 subjects showed that Mudan granule significantly improved 2 h postprandial blood glucose, glycated hemoglobin, and Michigan Neuropathy Screening Instrument (MNSI) score (Xun and Liu, 2020). Notably, overall the studies of Mudan granule available have involved small sample sizes, short duration, poor methodological quality, and without clinically registered information. For these reasons, high-quality clinical evidence of the safety and efficacy of Mudan granule in individuals with type 2 diabetic peripheral neuropathy is required urgently. Our research team will provide such a high-quality randomized controlled trial (RCT) study. This study aims at presenting the methodologies and full details of the protocol.

## Methods/Design

### Study Objectives

The trial is conducted for assessment of safety and efficacy of Mudan granule with a combination of methylcobalamin in improving Michigan Diabetic Neuropathy Score (MDNS) and relieving clinical symptoms in patients with type 2 diabetic peripheral neuropathy. We presume the hypothesis that Mudan granule + Methylcobalamin is more potent and efficient than Placebo + Methylcobalamin in improving MDNS and alleviating the clinical symptoms of people with type 2 diabetic peripheral neuropathy. 402 clinically stable patients will be randomized into this trial within the 24 weeks period. Recruitment performs in out-patient clinical institutions.

### Study Design

To test our hypothesis, a double-blind, randomized, placebo-controlled, parallel-arm, multi-center trial is designed. Fourteen research cooperation centers in China will participate in the trial, including Peking Union Medical College Hospital, Beijing Hospital, Affiliated Hospital of Liaoning University of Traditional Chinese Medicine, Affiliated Hospital of Qingdao University, Chengdu University of Traditional Chinese Medicine, The Fourth People’s Hospital of Chongqing, Zhengzhou Yihe Hospital Affiliated to Henan University, Zhu Xianyi Memorial Hospital of Tianjin Medical University, The Third Hospital of Xi’an, Huashan Hospital Affiliated to Fudan University, Gansu Provincial People’s Hospital, Shenzhen Hospital of Guangzhou University of Traditional Chinese Medicine, and Affiliated Hospital of Changchun University of Chinese Medicine. This clinical trial was registered with clinicaltrials.gov; Registration Number for Clinical Trial: NCT04711980; Any changes related to the protocol will be presented there. Figure 1 displays the flow diagram of this study.

**FIGURE 1 F1:**
[figure not shown]
The flow diagram of this study.

### Inclusion Criteria

1. Meet the diagnostic criteria of type 2 diabetic peripheral neuropathy (Author Anonymous, 2018):(a). Have a history of T2DM.

–The definition (American Diabetes Association, 2021) of T2DM is that fasting plasma glucose ≥126 mg/dl (7.0 mmol/L)Fasting refers to no caloric intake for at least 8 h*

OR.Two-hour plasma glucose ≥200 mg/dl (11.1 mmol/L) during an oral glucose tolerance test. The test should be conducted as described in accordance with the World Health Organization using a glucose load containing the equivalent of 75 g of anhydrous glucose dissolved in water.*

OR.HbA1c ≥ 6.5% (48 mmol/mol).

The test should be conducted in a laboratory using a method that is National Glycohemoglobin Standardization Program-certified and standardized to the Diabetes Control and Complications Trial assay.*

OR.In patients with typical symptoms of hyperglycemia or hyperglycemic crisis, a random plasma glucose ≥200 mg/dl (11.1 mmol/L).*

* without the presence of unequivocal hyperglycemia, the examination needs to be repeated twice.(b). Neuropathy occurs at or after the diagnosis of T2DM.(c). The presence of symptoms and signs should be aligned with the manifestations of DPN.(d). In patients with clinical symptoms (pain, numbness, paresthesia, etc.) of DPN, necessitating the need for abnormalities in one or more of the five examinations (stress perception, vibration perception, temperature perception, pain and ankle reflex); In patients without clinical symptoms of DPN, necessitating the need for abnormalities in two or more of the five examinations (stress perception, vibration perception, temperature perception, pain and ankle reflex).(e). All those with neuropathy resulting from other causes must be excluded.2. Meet the diagnostic criteria of TCM syndrome of Qi deficiency and collaterals obstruction syndrome.

Diagnostic Criteria of Qi deficiency and collaterals obstruction syndrome (Zheng, 2002):(a). Primary symptoms and signs: ① numbness; ② pain; ③ paresthesia(b). Secondary symptoms and signs: ① scaly dry skin; ② dim complexion; ③ fatigue; ④ spiritlessness and talking laziness; ⑤ spontaneous sweating(c). Tongue condition: light-dark/petechiae tongue, with thin and white coating.(d). Pulse condition: thin and astringent pulse.

Patients with two or three primary symptoms, two or more secondary symptoms, and tongue pulse signs could be diagnosed as Qi deficiency and collaterals obstruction syndrome.3. The patients are aged 30–70 years.4. Conduction velocity achieved using electromyography assessments in 2 or more nerves have decreased.5. The patient provides signed informed consent.

### Exclusion Criteria

1. Patients have recently taken antioxidants such as vitamin E or vitamin C; acute infection; renal or hepatic insufficiency; acute complications of T2DM; serious cardio-cerebrovascular diseases; neuropathy due to long-term alcohol intake and other factors.2. Besides methylcobalamin, drugs such as alpha lipoic acid, epalrestat, VitB12, Chinese patent medicine and decoction have been used to treat DPN within 4 weeks before enrollment.3. Poor control of blood pressure (systolic blood pressure greater than160 mmHg or diastolic blood pressure greater than 100 mmHg).4. Suffering from diabetic ketosis, ketoacidosis and serious infection within one month.5. Patients with comorbidities such as cardiovascular, renal, hepatic, and hematopoietic system and other severe primary diseases; serum transaminase over the normal value more than 2 times; serum creatinine greater than the upper limit of normal; psychiatric disorders.6. Pregnancy, ready to be pregnant or lactating female patients.7. With a history of multiple drug allergies or being allergic to the ingredients of Mudan granule.8. Participate in other clinical studies within one month.9. Alcohol abuse and/or taking psychoactive substances, drug abusers and dependents over the last five years.10. With a history of active ophthalmopathy, ocular surgery, glaucoma, acute or chronic corneal diseases, extended-wearing contact lens and so on.

### Withdrawal Criteria

#### The Withdrawal Decided by the Researcher

The researcher can decide to withdraw a subject from the study under the following circumstances:1. During the study, the subjects may develop severe acute or chronic complications or special physiological changes (e.g., human chorionic gonadotropin test is positive) that not appropriate for this study.2. During the study, the subjects may have poor adherence to medications, such as failure to take less than 80% or more than 120% of the prescribed dosage.3. Other treatment drugs were added without following the researcher’s guidance during the entire study period.

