### Subjects Withdrawal at Their Own Will

Based on the informed consent form, the subjects are free to withdraw from the trial at any point. Subjects who do not formally withdraw from the trial but no longer receive drugs and undergo testing or who are lost to follow-up are also regarded as withdrawn. The reasons for the subjects withdrawing should be ascertained and recorded wherever possible.

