## Efficacy Outcomes

### Primary Outcomes

Changes in total score on the MDNS Scale: The changes of MDNS will be compared in the two groups prior to and following Mudan granule administration. The total score is 46, ranging from 0 (least severe) to 46 (most severe). Measurement will be performed at baseline and week 12, 24.

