### Statistical Analysis

#### Definition and Selection of Statistical Analysis Data Set

The subjects in the trial will be categorized as follows:1. Full Analysis Set (FAS)

FAS is defined as the data set composed of all subjects who are block randomized and have at least one efficacy evaluation result after baseline, which is the main analysis set for efficacy evaluation. Demographics and other baseline characteristics are also set as the FAS. The missing value of the primary efficacy indicators will be filled with the last observation carried forward. In comparison, the missing values of secondary efficacy and safety indicators will not be filled.2. Per Protocol Set (PPS)

PPS comprises all the FAS subjects who meet the inclusion criteria but not the exclusion criteria and complete the treatment protocol without seriously violating the study protocol, which is the secondary analysis set for efficacy evaluation.3. Security data set (Safety Set, SS)

SS includes all subjects who are block randomized, receive at least one dose of Mudan granule, and have at least one postbaseline safety evaluation.

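### Researcher-decided withdrawal for poor adherence or unguided added drugs is from the study, with no MDNS assessment provided afterwards, so primary data are lost unnecessarily and filled by LOCF

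*Protocol article*

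**What the plan says.** Under the heading on withdrawal decided by the researcher, the Protocol article states: "The researcher can decide to withdraw a subject from the study under the following circumstances". Three circumstances follow. The second is that "the subjects may have poor adherence to medications, such as failure to take less than 80% or more than 120% of the prescribed dosage". The third is "Other treatment drugs were added without following the researcher’s guidance during the entire study period".

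The next section, on subjects leaving of their own will, adds that those who do not formally withdraw but "no longer receive drugs and undergo testing or who are lost to follow-up are also regarded as withdrawn".

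On the schedule, Primary Outcomes says of MDNS: "Measurement will be performed at baseline and week 12, 24". Secondary Outcomes schedules the TCM syndrome score every 4 weeks from week 4.

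On the analysis, the section defining the data sets puts into the FAS all randomised subjects who "have at least one efficacy evaluation result after baseline, which is the main analysis set for efficacy evaluation". It fills missing primary values by LOCF. It also defines a PPS, as the secondary efficacy set, limited to FAS subjects who finish treatment without a serious violation.

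Sample Size Calculation expects withdrawal of no more than 20%. Current Status says that recruitment has not begun.

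**The concern.** Stopping study medication and leaving the study are different events. The first describes what happened to treatment; the second ends data collection. The article names only the second, and triggers it by behaviour after randomisation.

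Poor adherence and self-added drugs are plausibly related to how the subject is doing. Someone who tolerates the granules badly may skip doses, and someone who feels no benefit may look for another treatment. That link is a reasoned inference; the document does not state it. If it holds, the missing MDNS values are not a random sample, and the primary analysis replaces them with earlier ones.

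The loss is also avoidable. The visits are already scheduled, and the PPS already exists to show the result among subjects who kept to the protocol. Assessments not made during the trial cannot be recovered by a later analysis.

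**Working it through.** **1. What happens to a withdrawn subject, by timing** (MDNS at baseline, weeks 12 and 24; TCM score from week 4):

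| Withdrawn | MDNS lost | Value used |
|---|---|---|
| Before any post-baseline efficacy result | weeks 12 and 24 | none; outside the FAS |
| After the week-4 visit, before week 12 | weeks 12 and 24 | in the FAS through the TCM score; only baseline MDNS is available to carry forward, i.e. zero change |
| After week 12 | week 24 only | week-12 value carried forward |

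Most of these subjects therefore stay in the FAS with an imputed MDNS.

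**2. The plan's own allowance.** 167 × 1.20 = 200.4, rounded up to 201 per group, which reproduces the stated target. If 20% are withdrawn and not assessed, 201 × 0.80 = 160.8, or about 161 observed week-24 values per group, fewer than the stated 167. This is the whole allowance; the article gives no share for adherence or added drugs. How 167 was obtained is a separate matter and is not used here.

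**3. Illustration of the shift under no true effect.** Assumptions, none of them in the document:
- both arms improve by I points by week 24;
- 60% of that is reached by week 12;
- half of withdrawals fall before week 12 (zero change carried forward) and half after it (0.6 × I carried forward);
- all withdrawn subjects remain in the FAS and would have followed the common course.

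With withdrawal proportion w, the mean improvement under LOCF is

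I × [(1 − w) + w × (0.5 × 0 + 0.5 × 0.6)] = I × (1 − 0.7 × w).

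The false difference between arms is therefore 0.7 × I × (difference in w). For 20% against 15%:

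| Common improvement I | Shift (points) | Share of 0.58 |
|---|---|---|
| 1 | 0.7 × 1 × 0.05 = 0.035, about 0.04 | 6% |
| 2 | 0.7 × 2 × 0.05 = 0.07 | 12% |
| 4 | 0.7 × 4 × 0.05 = 0.14 | 24% |

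A simulation on the same assumptions gave 0.04, 0.07 and 0.14. At equal rates the shift is 0. The factor 0.7 depends on timing, so equal rates with different timing would also leave a difference. The direction follows the arm that loses more subjects: that arm looks worse.

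**4. A second assumption set.** If all withdrawals come after week 12 and both arms improve by 1 further point between weeks 12 and 24, 10% against 20% gives 1 × (0.20 − 0.10) = 0.10 points. Equal rates of 20% give 0.

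**5. The adherence sentence.** Read literally, failing to take less than 80% means taking 80% or more, and the sentence offers this as an example of poor adherence. It contradicts its own purpose.

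**The case against.** Several objections stand and limit the point.

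- *A reader might infer that the rule builds per-protocol selection into the FAS.* The documents do not support this. Anyone with a post-baseline efficacy result stays in the FAS, and TCM scores begin at week 4. The problem is mainly imputed values, not removal from the set.
- *A reader might expect withdrawal to differ by arm because the granules are bitter.* The Blinding section says that the placebo was made to match the drug in look and taste, and that researchers and subjects are blinded. This limits unequal withdrawal without excluding it, and nothing in the article shows that rates will differ.
- *A reader might take any added drug as a trigger.* Only drugs added without the researcher's guidance count.
- *The shifts above measure LOCF under total withdrawal.* That total includes voluntary withdrawal, loss to follow-up and medical reasons. The share due to this rule is unknown, and keeping assessments would not recover subjects who withdraw consent.
- *The rule is permissive.* Its extent is therefore unknown and may vary by centre.
- *The section on voluntary withdrawal can be read as requiring both no drug and no testing,* which leaves room for subjects who are off drug but still tested. A fuller protocol might also provide for follow-up.

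The last objection does not remove the point. The article does state a level of withdrawal, and it is the study. Room for another reading is not a provision to assess these subjects.

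**Conclusion.** The point holds as a cheap improvement that should be made before recruitment. The stated rule lets researchers end participation after post-randomisation events that the PPS already handles, and LOCF then stands in for week-24 MDNS, or for both post-baseline values if withdrawal precedes week 12. The FAS comparison and its precision are weakened by an amount that cannot be fixed from the document.

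It would go too far to say that the FAS no longer protects the randomised comparison, or that bias of a given size will occur. In the illustration, null bias needs a difference between arms in the rate or timing of withdrawal. A 5-point difference gives 0.04 to 0.14 points over common improvements of 1 to 4 points, all assumed. The adherence wording is an editorial matter.

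**What to change.** Amend the withdrawal section to state that:

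1. poor adherence, or a drug added without the researcher's guidance, is recorded as a protocol deviation or a treatment discontinuation, not as withdrawal from the study;
2. such subjects still attend the scheduled week-12 and week-24 MDNS assessments unless they withdraw consent;
3. all observed MDNS values enter the FAS analysis, and adherence is examined through the existing PPS.

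Reconcile the 80%/120% sentence so that it says what is meant. Whether treatment stops in these cases is for the sponsor and is not addressed here.

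The cost is protocol wording, a few more already scheduled visits for subjects off treatment or not adhering, and a somewhat diluted effect estimate, since off-treatment outcomes are counted. Missing values from withdrawn consent and loss to follow-up would remain.

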### Subjects Withdrawal at Their Own Will

Based on the informed consent form, the subjects are free to withdraw from the trial at any point. Subjects who do not formally withdraw from the trial but no longer receive drugs and undergo testing or who are lost to follow-up are also regarded as withdrawn. The reasons for the subjects withdrawing should be ascertained and recorded wherever possible.

### Intervention Measures

All included subjects will accept conventional therapies containing 0.5 mg oral methylcobalamin tablets three times per day, lifestyle interventions, and other oral drugs to achieve stabilization of blood sugar, blood pressure, and lipids depending on American Diabetes Association guidelines. Subjects will be randomly allocated to either the intervention group (Mudan granule 7 g/bag, three times per day) or the control group (placebo 7 g/bag, three times per day) through a central randomization system. Treatment will continue for 24 weeks.

